# Letrozole ovulation regimen for frozen-thawed embryo transfer in women with polycystic ovary syndrome: study protocol for a randomized controlled trial

**DOI:** 10.1186/s13063-024-08164-z

**Published:** 2024-06-06

**Keywords:** Polycystic ovary syndrome, Letrozole, Programmed regimen, Frozen-embryo transfer, Clinical pregnancy rate

## Abstract

**Background:**

Women with polycystic ovary syndrome (PCOS) are usually selected to undergo an ovulation induction regimen or a programmed regimen for endometrial preparation in the frozen-thawed embryo transfer (FET) during their IVF/ICSI treatment. The programmed regimen permits flexible scheduling of embryo transfer but requires long-term usage of exogenous estrogen and higher dosages of luteal support while the letrozole ovulation regimen needs lower dosages of luteal support only. Recently, multiple studies have shown that the letrozole ovulation regimen can improve pregnancy outcomes of FET in women with PCOS compared with the programmed regimen. However, most of these studies are retrospective, and prospective studies are urgently needed the evidence from the perspective study is insufficient.

**Methods/design:**

We are undertaking a multicentre, randomized, controlled clinical trial of an endometrial preparation regimen for FET in women with PCOS. The eligible women are randomly assigned to either the letrozole ovulation regimen or the programmed regimen for endometrial preparation. The primary outcome is the clinical pregnancy rate.

**Discussion:**

The results of this study will provide evidence for whether the letrozole ovulation regimen for endometrial preparation could improve pregnancy outcomes in PCOS women undergoing FET.

**Trial registration:**

Chinese Clinical Trial Registry ChiCTR2200062244. Registered on 31 July 2022.

**Supplementary Information:**

The online version contains supplementary material available at 10.1186/s13063-024-08164-z.

## Background

The application of frozen-thawed embryo transfer (FET) has significantly increased the live birth rate (LBR) and reduced the incidence of ovarian hyperstimulation syndrome (OHSS), especially in patients with polycystic ovary syndrome (PCOS) [1]. The ovulation induction regimen, programmed regimen, and natural regimen are the three regimens available for endometrial preparation in the frozen-thawed embryo transfer (FET). Patients with PCOS are frequently chosen to undergo an ovulation induction regimen or programmed regimen, as they typically experience irregular menstruation or ovulation disorders. The endometrium is prepared with programmed oestrogen and progesterone in the programmed regimen, allowing for flexibility in the timing of embryo transfer. However, if pregnancy is confirmed, it requires long-term use of exogenous estrogen and greater dosages of luteal support for at least 2 months. The ovulation induction regimen uses medicines such as letrozole, clomiphene, and human menopausal gonadotropin (HMG) to prepare the endometrium. The timing of embryo transfer may not be so flexible, but it only needs a lower dosage of exogenous luteal support. Even though all of these regimens are frequently used for endometrial preparation for PCOS patients, picking one over the others is still difficult.

Letrozole is a third-generation, highly specific aromatase inhibitor that decreases the concentration of estrogen in the blood by blocking the conversion of testosterone to estrogen. This alleviates the negative feedback on the pituitary and brain glands. Substantially, the pituitary gland is stimulated to secrete follicle-stimulating hormone which promotes follicle development. In recent years, letrozole has become the drug of choice for ovulation induction in FET because of its mono-ovulatory effect and its short half-life of about 48 h. Meanwhile, when letrozole alone fails to stimulate follicular growth, the timely addition of HMG can greatly reduce the incidence of cycle cancellation [2].

Several retrospective studies have found that letrozole administration in FET increased clinical pregnancy rate (CPR) and LBR [3–6] and decreased the incidence of hypertensive disorders of pregnancy in women with PCOS compared to the programmed regimen [7]. However, a single-centre, randomized, controlled clinical trial found no significant difference between the two regimens in terms of CPR and embryo implantation rate [8]. According to a recent meta-analysis, the ovulation induction regimen increased the LBR and reduced the risk of miscarriage, preeclampsia, and preterm labour in patients with PCOS when compared to the programmed regimen. In the subgroup analysis, on the other hand, they evaluated different ovulation regimens and found that the letrozole ovulation regimen achieved a higher CPR [9]. Therefore, further prospective research is required to confirm whether the letrozole ovulation regimen can achieve better pregnancy outcomes than the programmed regimen.

This study is a multi-centre randomized controlled clinical trial. It compares the efficacy and safety of the letrozole ovulation regimen with the programmed regimen in women with PCOS undergoing FET.

## Methods/design

### Design and setting

This study is a multicentre, randomized controlled, open-label clinical trial to evaluate whether the letrozole ovulation regimen for endometrial preparation can improve the clinical pregnancy rate in PCOS patients as compared to the programmed regimen. Patients are recruited from six hospitals, including Guangdong Provincial People’s Hospital, General Hospital of Ningxia Medical University, the Second Hospital of Hebei Medical University, Xiamen Maternal and Child Health Care Hospital, Hospital for Reproductive Medicine Affiliated to Shandong University, and Xiangya Hospital, Central South University, spreading across different Chinese provinces—Guangdong, Shandong, Fujian, Hebei, Hunan, and Ningxia Autonomous Region.

### Inclusion criteria

The inclusion criteria are as follows: Women diagnosed with PCOS according to the Rotterdam criteria [10] Women aged under 38 years Frozen embryos from the first and/or second oocyte retrieval cycles

### Exclusion criteria

The exclusion criteria are as follows:Women with a history of unilateral or bilateral ovarian surgery.Women with a history of recurrent spontaneous abortion.Women with a uterine cavity abnormality, such as double uterus, uterine septum, and moderate and severe intrauterine adhesion.Chromosome abnormality (except chromosomal polymorphism) of either partner.A preimplantation genetic test is required.

The patients will be randomized (1:1) to the letrozole ovulation regimen group or the programmed regimen group in the FET cycle, and their pregnancy and perinatal outcomes during this cycle will be followed up and analysed. The flowchart will follow the study protocol as shown in Fig. 1. The items of this trial can be found in the WHO Trial Registration Data Set as shown in Additional file 1.

**Fig. 1 Fig1:**
[figure not shown]
Study flowchart

### Sample size

The PASS software version 15.0.5 (NCSS, LLC, Kaysville, UT, USA) was used to estimate the sample size. We assumed that the clinical pregnancy rate is 65% in the letrozole ovulation regimen group and 40.8% in the programmed regimen group based on past retrospective investigations [6]. To detect an absolute difference in CPRs, the study will involve 66 women in each group with a power of 80% and an alpha error of 0.05. Considering a 10% follow-up drop-out rate, our target sample size will be 148 women.

To minimize the loss of follow-up, we optimize our strategies of follow-up, including text messaging reminders to patients’ mobile phones the day before scheduled appointments, reducing the number of clinic visits if possible, and regular review of patients with missed appointments to allow early contact and intervention.

### Screening

We advertise for clinical study patient recruitment. PCOS patients who intend to undergo frozen embryo transfer will be screened according to inclusion and exclusion criteria. The eligible patients will sign informed consent after the assessment. The standardized case report forms are used to capture current medication status and previous medical history. Patients’ names are replaced with their phonetic initials to protect their privacy. A physical examination (height, body weight, waistline, hipline, blood pressure) and transvaginal ultrasound scan are performed. A diagnostic hysteroscopy is conducted on patients who are suspected of having an abnormal uterine cavity after an ultrasound scan. The serum basal sex hormones, anti-Müllerian hormone, glucose and lipid levels, and renal and hepatic function tested in the recent half year will be recorded. The research protocol, version 1.1, was finalized on May 30, 2022. The Standard Protocol Items: Recommendations for Interventional Trials (SPIRIT) figure (Fig. 2) shows the schedule for enrollment, interventions, and evaluation. The SPIRIT checklist is presented in Additional file 2.

**Fig. 2 Fig2:**
[figure not shown]
SPIRIT diagram for the schedule of enrollment, interventions, and assessments. ET, embryo transfer

### Randomization and blinding

A computer-generated random list is generated by SPSS 16.0 (SPSS Inc., Chicago, IL, USA). The statisticians will upload the random list into the online database’s central grouping system and maintain the random list absolutely confidential. The list is not accessible to the researchers. They are only given the group number when a patient is enrolled. Letrozole tablets or estradiol valerate tablets will be given to participants. Since the trial is open-label, neither the participants nor the physicians are blind to the group information, while all the generated data in the trial will be analysed by blinded independent biostatisticians.

### Interventions

#### Endometrial preparation

During menstruation, the endometrial preparation can begin if the follicles are less than 10 mm, and serum estradiol and progesterone are at the basic levels. Eligible patients are assigned at random to either the letrozole ovulation regimen or the programmed regimen.

Within 5 days of the menstrual cycle, women in the letrozole ovulation group will receive 2.5 or 5.0 mg of letrozole each day for 5 days. Around the 12th day of menstruation, serum hormone levels and ultrasound monitoring will be carried out. If there is no dominant follicle, low-dose HMG injections will be used to promote follicle growth. Human chorionic gonadotropin (HCG) ampules will be injected intramuscularly for the final oocyte triggering when the diameter of the dominant follicle measures at least 17 mm and the thickness of the endometrium measures at least 7 mm.

Within 3 days of menstruation, women in the programmed regimen group will take tablets containing 4–8 mg of estradiol valerate daily. After 10 days, an ultrasound will be used to determine the thickness of the endometrium and serum sex hormones will be measured. It is appropriate for shifting the endometrium when its thickness reaches 7 mm by administering dydrogesterone, Utrogestan, or Crinone either alone or in combination.

The FET cycle will be cancelled if the thickness of the endometrium in either group is less than 7 mm or if there is no follicle growth in the letrozole ovulation group even after the addition of HMG.

#### Embryo transfer and luteal support

A maximum of two blastocysts or embryos in the cleavage stage could be transferred. An experienced physician will carry out the embryo transfer, with trans-abdominal ultrasonography serving as guidance.

For luteal support, dydrogesterone 20 mg PO bid, Utrogestan 200 mg pv bid, and Crinone 90 mg pv qd are the most commonly prescribed medications. For patients in the letrozole ovulation group, one of them will be used starting on the day of ovulation. The transfer timing of frozen embryos is determined based on the time of ovulation. On the third day after ovulation, the D3 embryo will be transferred, and on the fifth day, the D5 embryo.

One or two drugs for luteal support will be administered to the patients in the programmed regimen group. If the pregnancy is confirmed, the use of luteal support and estradiol valerate tablets should be continued until 7–8 weeks of gestation, after which their dosages should be gradually decreased.

### Outcome and outcome assessments

The primary outcome is the clinical pregnancy rate, defined as the ratio of the clinical pregnancy (intrauterine gestation sac) number to the number of patients who received embryo transfer. The secondary outcomes include abortion rate, live birth rate, birth weight, pregnancy and perinatal complication, and neonatal complication.

Two weeks following embryo transfer, serum β-HCG is tested; a result of ≥ 10 IU/L indicates biochemical pregnancy. The patients who are biochemically pregnant will keep taking medications for luteal support. The existence of a gestational sac within the uterine cavity is referred to as clinical pregnancy. When the embryo implants anywhere other than the uterine cavity, it is referred to as an ectopic pregnancy. Around 5 weeks following embryo transfer, a transvaginal ultrasound is carried out to confirm clinical pregnancy. When a viable fetus with a fetal heartbeat is detected by ultrasound around 10 weeks following embryo transfer, it is considered to be an ongoing pregnancy.

Abortion rate is defined as the ratio of the number of nonviable pregnancies before 28 weeks of gestation to the number of clinical pregnancies. Abortion before 12 weeks of pregnancy is called early abortion while after 12 weeks of pregnancy is called late abortion. Live birth rate refers to the ratio of the number of normal fetuses delivered at 28 weeks or later of gestation to the number of patients who received embryo transfer. Preterm birth occurs between 28 and 37 weeks of gestation. A birth at 37 weeks or later is called a full-term birth. The congenital malformations are diagnosed after birth.

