### Data analysis

All the generated data in the trial will be analysed by blinded independent biostatisticians. The primary analysis will be performed according to the intention-to-treat (ITT) principle. The Statistical Package for the Social Sciences (version 24.0; SPSS Inc., USA) will be used for all analyses. All tests will be two-tailed, and a *P* value < 0.05 is considered to be statistically significant. The primary outcome, clinical pregnancy rate, will be analysed using the chi-square test. The secondary outcomes such as abortion rate, live birth rate, and some complications will be analysed using the chi-square test or Fisher’s exact test for expected frequencies less than 5. The other parameters will be analysed and compared according to the following methods. The Shapiro-Wilk test will be used to test the normal distribution of continuous variables. For normally distributed data, we will use Student’s *t*-test to examine the differences between groups; for non-normally distributed data, we will use the Wilcoxon rank-sum test. Continuous variables will be represented as means ± standard deviations. Categorical variables will be described as frequencies or percentages, and the chi-square test or Fisher’s exact test is used to examine the differences between groups.

We will perform a secondary per-protocol analysis according to the actual treatment that subjects received who comply with the protocol. The data analysis methods are as above.

Missing data will be treated as missing at random and will be imputed using the last observation carried forward method. For the missing values, a sensitivity analysis will be done under the hypothesis of the worst and the best outcomes for each missing individual. Therefore, all secondary per-protocol analysis outcomes will be considered exploratory. All statistical analyses will be done using the statistical package SPSS (version 24.0; SPSS Inc., USA).

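### The primary outcome is counted per woman transferred, but the primary analysis is called intention-to-treat and cycles can be cancelled after randomisation

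*Protocol article*

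**What the plan says.** Four statements in the protocol article bear on this.

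- **Outcome and outcome assessments:** the clinical pregnancy rate is "defined as the ratio of the clinical pregnancy (intrauterine gestation sac) number to the number of patients who received embryo transfer". The live birth rate is also divided by the number of women transferred.
- **Data analysis:** "The primary analysis will be performed according to the intention-to-treat (ITT) principle". The test is a two-sided chi-square at 0.05. A secondary per-protocol analysis follows the treatment actually received.
- **Endometrial preparation:** "Eligible patients are assigned at random to either the letrozole ovulation regimen or the programmed regimen". Letrozole or estradiol starts after that.
- **Endometrial preparation, last paragraph:** the cycle is cancelled in either arm if the endometrium is thinner than 7 mm, or "if there is no follicle growth in the letrozole ovulation group even after the addition of HMG".

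The Sample size section assumes that the "clinical pregnancy rate is 65% in the letrozole ovulation regimen group and 40.8% in the programmed regimen group" and adds 10% for loss to follow-up. It makes no allowance for cancelled cycles and does not say whether the assumed rates are per transfer or per woman randomised.

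**The concern.** Randomisation protects a comparison of all women allocated. It does not protect a comparison of those who later reach transfer, because reaching transfer depends on how each woman responds to the assigned regimen. One cancellation route is shared and the other exists only under letrozole, so the two transferred groups may be selected differently.

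The outcome definition and the analysis principle also give different instructions for the same woman. If she is randomised and her cycle is cancelled, intention-to-treat keeps her and the outcome definition leaves her out. The article has no rule that settles this. Last observation carried forward and the best/worst-case analysis deal with missing outcomes, and she is not missing: she is outside the definition. The 10% allowance is for loss to follow-up.

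The Design and setting section asks whether the letrozole regimen can raise the clinical pregnancy rate in women with PCOS. A cycle that fails during preparation is part of the answer to that question. At stake is whether a difference in the primary endpoint reflects the regimens or the selection of women counted.

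**Working it through.** **1. The plan's own figure.** Inputs from the Sample size section: p1 = 0.65, p2 = 0.408, difference d = 0.242, two-sided alpha 0.05, power 80%. With mean rate p = 0.529 and pooled variance:

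n = [1.960 × √(2 × 0.529 × 0.471) + 0.842 × √(0.65 × 0.35 + 0.408 × 0.592)]² / 0.242²
= [1.384 + 0.576]² / 0.0586 = 65.6, so 66 per arm.

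66 / 0.90 = 73.3, so 74 per arm and 148 in total. The stated figures reproduce. The sample-size arithmetic is not at fault.

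**2. Effect of the denominator when the regimens do not differ.** The documents give no cancellation rate, so the rates below are assumptions. Let the true clinical pregnancy rate per woman randomised be 45% in both arms, with 74 randomised per arm, and let a cancelled cycle yield no pregnancy. With cancellation share c:

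per-transfer rate = 0.45 / (1 − c); women transferred = 74 × (1 − c), rounded.

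The rejection probability of the two-sided chi-square test (no continuity correction) comes from exact enumeration of both binomial counts.

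| Cancelled, letrozole / programmed | Women transferred | Per-transfer rates | Difference (points) | Rejection |
|---|---|---|---|---|
| 0% / 0% | 74 / 74 | 45.0% / 45.0% | 0 | 5.7% |
| 5% / 5% | 70 / 70 | 47.4% / 47.4% | 0 | 5.1% |
| 5% / 0% | 70 / 74 | 47.4% / 45.0% | +2.4 | 6.6% |
| 15% / 5% | 63 / 70 | 52.9% / 47.4% | +5.6 | 10.2% |
| 20% / 5% | 59 / 70 | 56.3% / 47.4% | +8.9 | 17.5% |
| 5% / 15% | 70 / 63 | 47.4% / 52.9% | −5.6 | 10.2% |

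A plus sign favours letrozole. The baseline differs slightly from 5% because the counts are discrete. Equal cancellation leaves no spurious difference in this model. The sign follows whichever arm loses more women.

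**3. Power if all randomised women are counted.** Suppose the Sample size rates are per transfer. The per-randomised rate is then the assumed rate × (1 − c). Power at 74 per arm, by the same exact enumeration:

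- 0% / 0%: 65.0% vs 40.8%, power 86%
- 5% / 5%: 61.8% vs 38.8%, power 82%
- 10% / 5%: 58.5% vs 38.8%, power 70%
- 15% / 5%: 55.3% vs 38.8%, power 55%

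The normal approximation used in step 1 gives slightly lower values: 84.6%, 80.5%, 67.4% and 52.0%. These figures use all 74 per arm and leave no room for loss to follow-up.

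**The case against.** **A reader might infer that the rule favours letrozole**, because only that arm has a second cancellation route. The documents do not support this. They give no cancellation rate by arm or reason, and an additional route does not establish a higher total. The thin-endometrium route is shared and could cancel more programmed cycles. The Background adds that timely HMG can greatly reduce cancellation. The 5% / 15% row shows the bias reversed.

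**The effect may be small.** With equal or nearly equal cancellation, the false-positive rate barely moves. Even the largest scenario shown, 8.9 points, is well below the planned 24.2. This stands as a limit on size. It does not remove the conflict, since nothing in the text keeps cancellation equal or low.

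**Intention-to-treat can be read loosely as analysis by allocated arm.** The Data analysis section does contrast it with treatment actually received, and transferred women analysed as allocated would fit that reading. Such a set is a modified intention-to-treat population, so the label would still be wrong.

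**A fuller protocol or an analysis plan may define the population.** That excuses matters the article leaves out. Here the article prints both the denominator and the principle, and they disagree on the primary endpoint.

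**The abortion rate might seem open to the same criticism**, because it is counted per clinical pregnancy. It is a secondary outcome and usable as a descriptive measure, and the intention-to-treat sentence concerns the primary analysis. It can stay.

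**Conclusion.** The concern holds as a conflict between the primary outcome's denominator and the stated intention-to-treat analysis, and it must be fixed. As written, the primary comparison is restricted to women who reach transfer, an event after randomisation that the regimen can affect. Live birth has the same defect.

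Neither the direction nor the size of the bias can be stated. Under the assumptions shown (45% per randomised woman in both arms, 74 per arm), the spurious difference runs from −5.6 to +8.9 points. The rejection probability runs from 5.1% to 17.5%, against 5.7% with no cancellation. Those ranges depend wholly on the assumed cancellation shares. The conflict does not depend on them. The clinical cancellation rule itself is not in question.

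**What to change.** Make the change in a dated amendment before any unblinded comparison of the arms. The trial is open-label and about half the women were enrolled when the article was written, so it should not wait for database lock.

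- Define clinical pregnancy and live birth as women with the event from the randomised FET cycle, divided by all women randomised, by allocated group. Count a cancelled cycle or no transfer as no event.
- Keep the per-transfer rates as labelled secondary analyses.
- Tabulate cancellations and non-transfers by arm and reason.
- State whether the Sample size rates are per transfer or per woman randomised, and restate power on per-randomised rates with an explicit cancellation assumption.

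No new outcome data are needed. The cost is that headline rates fall wherever cycles are cancelled, and power may fall too. If the assumed rates are per transfer, power at 74 per arm drops below 80% in the two scenarios of step 3 where letrozole loses more cycles. The sponsor should therefore recheck the sample size, which the article's Trial status section suggests was still possible because enrolment was continuing.

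### Live birth rate is defined as fetuses delivered per woman transferred, which is not the proportion of women that the planned chi-square or Fisher test requires once twins occur

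*Protocol article*

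**What the plan says.** Three statements in the protocol article bear on this point.

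- **Definition** (Outcome and outcome assessments). The defining sentence begins: "Live birth rate refers to the ratio of the number of normal fetuses delivered at". It sets a threshold of 28 gestational weeks and divides by the women who had a transfer. The numerator counts fetuses and the denominator counts women.
- **Embryos per transfer** (Embryo transfer and luteal support). "A maximum of two blastocysts or embryos in the cleavage stage could be transferred".
- **Test** (Data analysis). "The secondary outcomes such as abortion rate, live birth rate, and some complications will be analysed using the chi-square test". When expected frequencies fall below 5, Fisher's exact test takes its place.

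In the same outcome section, the primary outcome counts clinical pregnancies per woman transferred, and the abortion rate counts nonviable pregnancies per clinical pregnancy. Among these three rates, only the live birth rate has a numerator counted in fetuses. The section also states that "The congenital malformations are diagnosed after birth", but it does not say what makes a fetus normal.

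**The concern.** A chi-square or Fisher test on a 2×2 table needs independent units, each scored yes or no. Under the stated definition a woman can score 0, 1 or 2. Three things follow if the definition is applied literally.

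- The variance of the ratio is larger than the test assumes, because two fetuses of one mother arrive together. The p-value is then too small.
- The measure moves with twinning. An arm with more twin deliveries, but no more women taking a baby home, appears to have a higher live birth rate.
- In the extreme, fetuses can outnumber women, and no 2×2 table exists.

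The wording also leaves the event itself open. The qualifier for normal could be read to leave out a live-born infant with a malformation, and the sentence does not say that the infant must be born alive. Live birth is the secondary outcome of most direct interest to patients, so both its unit and its event should be unambiguous.

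**Working it through.** **The plan's own figure.** The document gives no calculation for live birth. Its one sample size calculation, for the primary outcome, reproduces. With 65% against 40.8%, two-sided 5%, 80% power and pooled variance without continuity correction:

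- mean proportion = 0.529
- n = [1.960·√(2·0.529·0.471) + 0.842·√(0.65·0.35 + 0.408·0.592)]² / 0.242² ≈ 65.6, so 66 per arm
- 66/0.9 = 73.3, so 74 per arm and 148 in total

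The present point does not touch that figure.

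**Inputs for the check.** From the document: up to two embryos, 66 women per arm, two-sided 5%. Assumed, because the document gives neither: the proportion p of women who deliver, and the share t of deliveries that are twins. All women counted are taken to have had a transfer, and all fetuses delivered are taken as normal and live-born.

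**Variance of the stated ratio.** Fetuses per woman equal 0 with probability 1−p, 1 with probability p(1−t) and 2 with probability pt. Hence:

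- mean m = p(1+t)
- true variance = p(1−t) + 4pt − m² = p(1+3t) − m²
- variance assumed by a test of proportions = m(1−m)
- large-sample rejection rate under no difference = 2·[1 − Φ(1.960·√(assumed/true))]

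With p = 45%:

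| Twin share t | m | True variance | Assumed variance | Ratio | Rejection rate, formula | Rejection rate, simulated |
|---|---|---|---|---|---|---|
| 5% | 0.4725 | 0.294 | 0.249 | 1.18 | 7.1% | 6.6% |
| 10% | 0.495 | 0.340 | 0.250 | 1.36 | 9.3% | 8.7% |
| 20% | 0.540 | 0.428 | 0.248 | 1.72 | 13.6% | 13.1% |
| 25% | 0.5625 | 0.471 | 0.246 | 1.91 | 15.7% | 15.4% |

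The simulated column is 400,000 trials per row, 66 women per arm, chi-square without continuity correction. In the same trials, counting women with at least one delivery gave 4.5% to 4.6%.

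**Wider range.** With delivery proportions of 30% to 60% and twin shares of 10% to 40%, simulation (100,000 trials per setting) gave 8% to 37% for the ratio as written and 4.5% to 5.1% for the count of women.

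**Artefact from twinning.** Let 45% of women deliver in both arms, with twins in 30% of deliveries in one arm and 15% in the other:

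- 0.45 × 1.30 = 58.5%
- 0.45 × 1.15 = 51.75%

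The 6.75-point difference consists only of second twins.

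**Can fetuses exceed women?** At 60% delivering and 40% twins, this happened in at least one arm in about 8% of simulated trials. At 45% delivering and up to 25% twins, it did not happen in any of the 400,000. It is a limiting case and not the main problem.

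**The case against.** The strongest reply is that the authors probably meant women with a live birth. The denominator is patients, the neighbouring rates count pregnancies, and a chi-square test naturally takes one yes or no per woman. If the analysis is done that way, the test keeps its size. This is a fair inference about intent, and it makes the inflated error rate conditional on literal use of the definition. It does not rescue the text: the article states a definition and names a test, and the two do not fit. This is therefore not a detail left to a fuller document.

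The reply is also right that twinning may be uncommon. Two embryos is a maximum, and the document gives no share of double transfers. At 5% twins the excess is about two percentage points.

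Several stronger readings are tempting and are not supported.

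- *Stillbirths are to be counted as live births.* The sentence omits live-born, but the outcome's name points the other way. This is loose wording and not a rule.
- *Malformations will lower the live birth rate.* The qualifier is undefined, and the remark on when malformations are diagnosed does not say that such infants leave the numerator. Ambiguity is all that can be claimed.
- *The birth weight test is invalid for the same reason.* Birth weight is listed as an outcome ("The secondary outcomes include abortion rate, live birth rate, birth weight, pregnancy and perinatal complication, and neonatal complication") and falls under the general rule for continuous variables ("for non-normally distributed data, we will use the Wilcoxon rank-sum test", otherwise a t-test). No unit is stated. Either test is sound for singletons or for one value per mother, and the unit can be set elsewhere.
- *The denominator must become all randomised women.* That is a separate question about the intention-to-treat population, and the mismatch of units does not settle it.

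**Conclusion.** The point holds as a defect in the stated definition of a secondary outcome. Fetuses over women, with up to two embryos transferred, is not a proportion of women, and the planned chi-square or Fisher test does not apply to it once twins occur. If the ratio is tested as written with 45% of women delivering, the nominal 5% test rejects in about 7% of null trials at 5% twins, rising to 15–16% at 25% twins. Unequal twinning would add a spurious difference in whichever arm has more twins. These sizes rest on assumed delivery and twin rates and on literal use of the definition. The undefined qualifier and the missing requirement of live birth are secondary ambiguities in the same sentence. The primary outcome, its test and the sample size of 148 are unaffected. This should be fixed before analysis, but it does not threaten the trial's main conclusion.

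**What to change.** Redefine the numerator as the number of women with at least one live-born infant at or after the protocol's existing 28-week threshold, regardless of malformation, each woman counted once. The planned chi-square or Fisher test can then stand. Report multiple births, stillbirths and malformations separately by arm, so that twinning and infant safety are visible in their own right and are not mixed into an efficacy measure.

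The cost is one sentence, recorded as an amendment or in the analysis plan before the data are analysed by arm. The Follow-up plan already collects obstetric and neonatal records at delivery and neonatal complications at 6 weeks, so no new data and no change in sample size are needed.
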